### Informed Consent

Inclusion will be feasible after patient approval, relative approval, or an emergency consent procedure (according to Italian law). The consent forms are available from the corresponding author on request. Day 0 will be considered the day of enrollment.

### Additional Consent Provisions

Informed consent approval includes agreement for the collection of biological specimens in ancillary studies, which will be stored for a maximum duration of 15 years.

### Outcomes

#### Primary Endpoint

The hypothesis is that monocytes, NK cells, and CD4^+^ and CD8^+^ T cells in patients with severe SARS-CoV-2 infection will show functional impairment. Moreover, innate cells will reveal overpowering hyperactivity, while adaptive T cells will show an impairment of activity that can provoke a pathologic inflammatory response with massive production of proinflammatory cytokines, edema, and pulmonary fibrosis.

#### Secondary Endpoints

The secondary endpoints are to correlate clinical data and vaccination history with laboratory immune patterns to identify protective factors for severe COVID-19 and break new ground for advanced therapeutic strategies.

Identifying differences between patients having mild infection with positive outcomes and patients having ARDS requiring ventilatory assistance could be useful to optimize the therapy and to come up with an immunostimulant therapy that can produce specific immunity and can decrease the hyperactivity of the innate response and thus the inflammatory condition.

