#### Secondary Objectives

The secondary objectives are to identify protective factors, using anamnestic data, such as preceding vaccinations, comorbidities, clinical presentation of COVID-19 in terms of clinical signs and symptoms, and biochemical findings. The recognition of a population of patients safe from excessive inflammation against SARS-CoV-2 could define a risk score for the severity of COVID-19, which could allow for the best clinical choice tailored to each patient. Moreover, favorable immunological pattern identification could be followed by implementation of prophylactic or therapeutic immunomodulatory treatments.

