### Recruitment

The proposed study aims to analyze patients with confirmed SARS-CoV-2 infection by real-time reverse transcription polymerase chain reaction (RT-PCR) assays on throat swabs in order to identify differences in their immune responses. Patients will be recruited at the Emergency Department of “Ospedale di Circolo – ASST Sette Laghi,” University of Insubria in Varese, Italy.

A control group of healthy people will be required for further comparison of the findings. We will consider healthy people (both males and females; aged ≥18 years) without infection (negative for SARS-CoV-2), without symptoms of infectious diseases (neither chronic nor acute), and without chronic pathologies (N=30).

After the informed consent procedure, the sample will be divided into 4 subgroups according to the severity of clinical impairment, with at least 30 people in each subgroup. The severity of pneumonia cases will be measured with SMART-COP (systolic blood pressure, multilobar chest radiography involvement, albumin level, respiratory rate, tachycardia, confusion, oxygenation, and arterial pH) [30-32]. The following 4 categories of patients positive for SARS-CoV-2 infection will be analyzed: (1) asymptomatic patients (AS19); (2) mildly symptomatic patients with fever, tiredness, dry cough, diarrhea, etc and without full-blown pneumonia (PAU19); (3) patients with a diagnosis of pneumonia with a “low” risk score (SMART-COP) (POL19); and (4) patients with a diagnosis of pneumonia with a “moderate/high” risk score (SMART-COP) (ARD19).

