### Participant Timeline

The estimated study duration is 6 months from the first to last patient recruitment. Each patient will remain in the study until discharge or death.

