The 4- to 5-day monocyte culture will be further stimulated for 24 h with LPS (Sigma Aldrich) and IFNγ (Miltenyi Biotec) (M1 stimulus) or IL-4 (Miltenyi Biotec) (M2 stimulus) to investigate macrophage polarization, with assessment of surface M1 markers (TNFα and CXCL10 [BD]) or M2 markers (IL-10 and CCL18 [BD]) to check the prevalence of macrophage polarization in different groups of COVID-19 patients.

The epidemiological analysis will be carried out by integrating both vaccination history and the daily data collected after hospital admission. Azienda a tutela della salute Insubria archives will provide missing data.

Considering the immunological profile, patients with COVID-19 will undergo routine examinations and the following: lymphocyte immunophenotyping; determination of C3 and C4 complement fraction activity; determination of serum immunoglobulin (IgG, IgM, IgA, and IgE) levels; serum protein electrophoresis; determination of serum angiotensin converting enzyme levels [36,37]; cytomegalovirus serology tests; and determination of serum IL-6 levels.

A specific data collection form will store information quickly, and then, data will be collected in a database.

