### Statistical Methods for the Primary and Secondary Outcomes

Associations between different variables will be examined using Pearson correlation coefficients. Paired comparisons will be made using the Wilcoxon matched pairs test. Nonpaired comparisons will be made using the 2-tailed Mann-Whitney test. Multiple comparisons will be made using appropriate one-way analysis of variance (ANOVA). A *P* value <.05 will be considered statistically significant. All statistical analyses will be performed using R version 3.4.3 (R Project for Statistical Computing) and SPSS 21 (SPSS Inc).

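### The secondary endpoint correlates vaccination history with immune patterns, but its aim is protection against severe COVID-19, and no stated analysis takes severity group as the response

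*Protocol article*

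**What the plan says.** Secondary Objectives gives the aim: "The secondary objectives are to identify protective factors, using anamnestic data, such as preceding vaccinations, comorbidities, clinical presentation of COVID-19", together with biochemical findings. It adds that recognising a patient population spared excessive inflammation "could define a risk score for the severity of COVID-19".

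Secondary Endpoints turns this into an endpoint: "The secondary endpoints are to correlate clinical data and vaccination history with laboratory immune patterns to identify protective factors for severe COVID-19". The next paragraph of that section adds: "Identifying differences between patients having mild infection with positive outcomes and patients having ARDS requiring ventilatory assistance could be useful". It attaches no factor and no test to that contrast.

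Under Recruitment, "the sample will be divided into 4 subgroups according to the severity of clinical impairment": AS19, PAU19, POL19 and ARD19, with a minimum of 30 in each. Sample Size fixes 30 per group, 120 patients in all, plus 30 healthy controls.

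Statistical Methods for the Primary and Secondary Outcomes says: "Associations between different variables will be examined using Pearson correlation coefficients". For other comparisons it names the Wilcoxon matched pairs test, the two-tailed Mann-Whitney test and one-way ANOVA, at P<.05. No regression or other adjusted method appears.

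**The concern.** A factor is protective against severe disease if, other things equal, people who have it are less often severely ill. That calls for severity as the response. The endpoint instead pairs vaccination history with a laboratory marker, which is at best one step on the way. If the plan is followed as written, the result is a set of unadjusted marker associations that could be reported as protection.

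Confounding makes this worse, and the Introduction itself names the confounders. It says that severe illness is nearly absent below 40 years, that fatality is almost twice as high in males, and that comorbidity explains part of the mortality pattern. It also argues that vaccine-induced protection fades with age. On the protocol's own account, then, age bears on both the exposure and severity.

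**Working it through.** **1. Aim, endpoint and method side by side**

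| Element | Protocol article | Severity is the response? |
|---|---|---|
| Aim | protective factors for severe disease | yes, by implication |
| Endpoint | clinical data and vaccination history correlated with immune patterns | no |
| Mild versus ARDS contrast | described as potentially useful for therapy | no factor or test attached |
| Epidemiological analysis | vaccination history combined with daily in-hospital data | no response or model named |
| Statistical methods | Pearson, Wilcoxon, Mann-Whitney, ANOVA | not specified; none adjusted |

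No row names vaccination history as factor with severity group as response.

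**2. Can the indirect route replace the direct one?**

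Let r1 be the vaccination-marker correlation and r2 the marker-severity correlation. The third correlation, vaccination-severity, must lie within

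r1·r2 ± √[(1 − r1²)(1 − r2²)].

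The protocol gives no correlations, so the inputs are assumptions:

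- Both 0.3: 0.09 ± 0.91, that is -0.82 to 1.00.
- Both 0.6: 0.36 ± 0.64, that is -0.28 to 1.00.
- Both 0.8: 0.64 ± 0.36, that is 0.28 to 1.00.

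For two equal correlations the sign is settled only when r² > 1 − r², which means r above √0.5 ≈ 0.71. These are algebraic limits. A yes/no history and a four-level group are too coarse to reach the extremes, but at moderate correlations even the direction stays open.

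**3. What the direct comparison could detect**

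The plan's own figure first: 4 × 30 = 120 is correct. The accompanying claim of detecting 20% to 30% differences concerns immune-cell phenotype and function. It cannot be reproduced, because no standard deviation or power is given, and it says nothing about vaccination against severity.

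For a yes/no vaccination history, 30 versus 30, two-sided 0.05:

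power = Φ{[|p1 − p2| − 1.96·√(2·p̄(1 − p̄)/30)] / √[(p1(1 − p1) + p2(1 − p2))/30]}, where p̄ is the mean of p1 and p2.

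Example with p1 = 0.50 and p2 = 0.165: p̄ = 0.3325. The standard errors are 0.1216 (null) and 0.1137 (alternative). Then (0.335 − 1.96 × 0.1216)/0.1137 ≈ 0.85, and the power is 80%.

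| Assumed higher rate | Lower rate at 80% power | Difference (points) |
|---|---|---|
| 0.50 | 0.165 | 33.5 |
| 0.70 | 0.345 | 35.5 |
| 0.80 | 0.457 | 34.3 |
| 0.90 | 0.591 | 30.9 |

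For ARD19 (30) against the other 90 patients, the same method gives about 23 to 29 points for higher rates of 0.50 to 0.90. These are unadjusted two-group figures.

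**The case against.** The strongest reply is that severity is built into the study. There are four severity groups, differences between severities are expected in the Primary Objective, and Secondary Endpoints mentions mild infection against ARDS. The clinical data in the endpoint could include severity, and the unpaired and multi-group tests could be run on vaccination history by group. A condensed article may also leave modelling detail to documents not shown here.

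Much of this stands. A reader might infer that the study never relates protective factors to severity, or that the secondary aim cannot be answered. The documents do not support either reading: the groups and generic tests exist, and for immune markers a comparison by severity is clearly intended. What remains is that the article does fix an endpoint, that endpoint does not match its aim, and every method it lists is unadjusted. That goes beyond omitted detail.

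Other tempting readings also go too far:

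- **Risk score.** It is a possible later product, not an endpoint. The worry that it would describe severity already present applies to day-0 blood markers, not to vaccination or comorbidity, which precede infection.
- **Unused outcome.** "Each patient will remain in the study until discharge or death", but leaving out an outcome model is ordinary in a condensed article. No section says that ventilatory assistance is recorded as an outcome.
- **Spurious pooled correlations.** Suppose two markers are independent within groups and each shifts by an assumed 0.5 SD per severity step. The between-group variance over four equal groups is 0.3125, and the pooled r is 0.3125/1.3125 ≈ 0.24. The article does not say that correlations are pooled over groups, so this is a hazard to exclude, not an error shown.
- **Biased vaccination source.** For vaccination history, the local health authority's "archives will provide missing data". Nothing says that completeness differs by severity. If archive records were more sensitive than self-report and were used more for severe patients, those patients would look more vaccinated, which would hide protection rather than create it.

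**Conclusion.** The point holds as a mismatch between aim and endpoint, compounded by unadjusted methods. As stated, the secondary endpoint can show that vaccination history and immune markers vary together; it cannot by itself show protection against severe COVID-19. With both intermediate correlations at an assumed 0.3, the correlation of interest is confined only to -0.82 to 1.00. The textual part rests on no assumption. The numerical parts rest on assumed correlations and vaccination rates, since the article gives none. The defect concerns the secondary aim, not the primary one, and should be corrected before the analysis is finalised.

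**What to change.** State that protective factors are assessed by relating the four severity groups (AS19, PAU19, POL19, ARD19) to vaccination history in an adjacent-category or multinomial logistic model, adjusted for age, sex and comorbidity. Sampling by severity group shifts only the intercepts of these models, so their slopes remain interpretable. The slopes of a proportional-odds model would not be protected in the same way.

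Keep the correlations with immune patterns as exploratory, reported within severity group or adjusted for it. Claim no absolute risk, because group sizes are set by quota, and describe any risk score as exploratory.

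Optionally, if completeness of vaccination history proves to differ by severity, take it from the archive for all patients, as the primary or a sensitivity analysis.

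The cost is analysis wording and, for the optional step, an archive query. Results reports that the clinical data set is complete and the immunological analysis is still running, so no new patients are needed. The downside is imprecision: with 30 per group only the large differences shown above are detectable, so a null result would not exclude a useful protective effect, and the covariates must be few.

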### Recruitment

The proposed study aims to analyze patients with confirmed SARS-CoV-2 infection by real-time reverse transcription polymerase chain reaction (RT-PCR) assays on throat swabs in order to identify differences in their immune responses. Patients will be recruited at the Emergency Department of “Ospedale di Circolo – ASST Sette Laghi,” University of Insubria in Varese, Italy.

A control group of healthy people will be required for further comparison of the findings. We will consider healthy people (both males and females; aged ≥18 years) without infection (negative for SARS-CoV-2), without symptoms of infectious diseases (neither chronic nor acute), and without chronic pathologies (N=30).

After the informed consent procedure, the sample will be divided into 4 subgroups according to the severity of clinical impairment, with at least 30 people in each subgroup. The severity of pneumonia cases will be measured with SMART-COP (systolic blood pressure, multilobar chest radiography involvement, albumin level, respiratory rate, tachycardia, confusion, oxygenation, and arterial pH) [30-32]. The following 4 categories of patients positive for SARS-CoV-2 infection will be analyzed: (1) asymptomatic patients (AS19); (2) mildly symptomatic patients with fever, tiredness, dry cough, diarrhea, etc and without full-blown pneumonia (PAU19); (3) patients with a diagnosis of pneumonia with a “low” risk score (SMART-COP) (POL19); and (4) patients with a diagnosis of pneumonia with a “moderate/high” risk score (SMART-COP) (ARD19).

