However, several mechanisms of trained immunity remain unclear, because the trained immune memory–like phenomenon appears to be for a few months or at least a few years. This immunity is not persistent but progressively fades out. Decreased immune response in the elderly could be responsible for more severe acute respiratory disease from coronaviruses in general and higher mortality from COVID-19, since SARS-CoV-2 can cause an explosive attack against the respiratory system, which is similar to major trauma and allows the development of acute respiratory distress syndrome (ARDS). No evident differences were found in different age groups among healthy people, which could justify the drop in immunity against coronaviruses, except its natural fadeout. The trained immune response acts from the age of 2 years, when hypothetical stimulation occurs, to the fifth decade because of its slow decrease.

Vaccines provide external stimulations in healthy people that trigger immune system responses (eg, diphtheria, tetanus, and pertussis [DTP] vaccines stimulate the immune system). Specific vaccines trigger specific immune actions against specific infectious agents, but provide sprouting immunity against antigens in transit, such as those of coronaviruses and other community-circulating viruses [6]. The underlying immunological phenomena are “bystander effect” and “trained immunity.”

Children receive vaccines during the first year of life. Consequently, they become protected against not only specific pathogens but also multiple antigens from pathogens in transit. The developed immunity gives protection against multiple viral infections for years until naturally fading out. After the fifth decade, this immunity is slower to be recalled and reactivated. At this point, a viral infection will find the immune system almost incompetent, and the virus can enter the organism and cause extensive damage. Among elderly people, severe pneumonia and ARDS are frequently noted when they have a coronavirus infection, flu, etc. The history of pandemic viruses reveals an unexplained phenomenon, which could support this hypothesis. In fact, the “Spanish flu” showed a higher mortality rate among young people, especially those aged 20 to 45 years, which could be partly explained by their life conditions after the end of the First World War.

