### Eligibility Criteria

The inclusion criteria will be checked before inclusion in the study. The inclusion criteria are as follows: age ≥18 years and documented SARS-CoV-2 infection, without sequencing to differentiate viral variants.

The exclusion criteria are as follows: refusal to the sign the agreement (informed consent); inability to sign the agreement; and HIV, hepatitis C virus, or hepatitis B virus (positive to hepatitis B surface antigen) infection.

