### Plans for the Collection, Laboratory Evaluation, and Storage of Biological Specimens

On day 0, blood samples (15 mL) will be drawn in EDTA tubes, centrifuged, and stored (−80°C) for subsequent analysis. After the first analysis, the remaining biological specimens will be kept for a maximum duration of 15 years.

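### The asymptomatic group (AS19) comes from the Emergency Department with no limit on other acute conditions, so its immune profile may be confounded by the reason for attendance

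*Protocol article*

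**What the plan says.** All points are from the protocol article.

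- **Source.** Under Recruitment: "Patients will be recruited at the Emergency Department of" the study hospital. No other route is named for infected patients, such as contact tracing, community swabbing or staff screening.
- **Group.** The same section lists the first of four severity groups as "1) asymptomatic patients (AS19". It does not say how these patients were found or why they were in the department. Sample Size sets 30 patients for this group out of 120 infected.
- **Eligibility.** Inclusion asks for "age ≥18 years and documented SARS-CoV-2 infection, without sequencing to differentiate viral variants". Apart from refusal of consent, the exclusions are "inability to sign the agreement; and HIV, hepatitis C virus, or hepatitis B virus (positive to hepatitis B surface antigen) infection". Concurrent acute illness, injury and recent surgery are not mentioned.
- **Controls.** The 30 healthy controls must be negative for the virus and "without symptoms of infectious diseases (neither chronic nor acute), and without chronic pathologies (N=30".
- **Timing.** "On day 0, blood samples (15 mL) will be drawn in EDTA tubes", and Informed Consent adds: "Day 0 will be considered the day of enrollment".
- **Analysis.** Statistical Methods for the Primary and Secondary Outcomes gives Mann-Whitney tests for unpaired comparisons, one-way ANOVA for multiple comparisons, and Pearson correlations. No adjustment or restriction for concurrent conditions is stated.

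**The concern.** A person without symptoms who is recruited in an Emergency Department may have come for another reason and been found positive on testing. If that reason was an injury, another infection or an acute inflammatory condition, it may itself affect the markers under study: monocyte and NK-cell activation, T-cell function and plasma cytokines. Blood taken on the day of enrollment is close in time to that event. Participant Timeline follows patients to discharge or death, and daily data are collected after hospital admission. This makes a separate reason for attendance plausible in at least some asymptomatic patients.

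The Primary Objective expects differences between patients of varying severity and healthy people, and AS19 is the least severe of the four groups. The Secondary Objectives look for patients spared excessive inflammation, and AS19 is an obvious place to look. A concurrent condition could widen the AS19 difference from controls. If it moved markers in the same direction as severe COVID-19, it could also narrow the difference from the moderate/high-risk pneumonia group (ARD19).

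**Working it through.** **1. What the article settles.** No stated figure is in dispute here. The group sizes agree: 4 × 30 = 120 infected, plus 30 controls. The question is what the stated source, criteria, timing and analysis allow when taken together.

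| Element | AS19 | Healthy controls |
|---|---|---|
| Source | Emergency Department | not stated |
| Infection | RT-PCR positive | negative |
| Acute infectious symptoms other than COVID-19 | no explicit limit | excluded |
| Injury, surgery, other acute illness | no explicit limit | must be healthy people |
| Chronic disease | only HIV, HCV and HBV excluded | excluded |

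So an AS19 patient with another acute condition can be enrolled, is sampled on that day, and enters an unadjusted comparison. The article gives neither the fraction of such patients nor the size of any marker shift.

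**2. Illustration of size.** Both inputs are assumptions:

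- q, the share of AS19 with another acute condition: 0.1 to 0.7
- d, the shift of a marker in those patients: 0.5 to 1 SD

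Shift of the AS19 mean = q × d

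- lowest: 0.1 × 0.5 = 0.05 SD
- highest: 0.7 × 1 = 0.7 SD

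**3. Effect on AS19 versus controls if infection itself had no effect.** Normal approximation, 30 against 30, two-sided 0.05:

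SE = √[(2 + q(1 − q)d²)/30]; P(significant) = Φ(qd/SE − 1.96) + Φ(−qd/SE − 1.96)

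| q | d (SD) | shift (SD) | SE | P(significant) |
|---|---|---|---|---|
| 0 | – | 0 | 0.258 | 5% |
| 0.1 | 0.5 | 0.05 | 0.260 | 5.4% |
| 0.5 | 0.5 | 0.25 | 0.262 | 16% |
| 0.5 | 1 | 0.50 | 0.274 | 45% |
| 0.7 | 1 | 0.70 | 0.271 | 73% |

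**4. Effect on AS19 versus ARD19.** Suppose the true difference is 1 SD, the shift is toward ARD19, and ARD19 carries no shift of its own (all assumed). The expected difference is 1 − qd:

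- lowest: 1 − 0.05 = 0.95 SD
- highest: 1 − 0.7 = 0.3 SD

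If concurrent conditions also occur in ARD19, or if they move a marker the other way, the narrowing is smaller or reversed.

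**The case against.** The strongest objection is that nothing in the article says why AS19 patients attended. They could have come as contacts, for a swab, or on referral after a positive test. On a plain reading, a patient with an acute abdomen or another infection is not asymptomatic at all. This stands: the article leaves the possibility of confounding open but does not show that it occurred.

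A reader might infer that AS19 patients were there for another illness or injury, and that the group therefore shows that condition's response and not silent infection. The text does not support this. Every infected patient is RT-PCR positive, so at worst two effects are mixed in an unknown fraction of the group.

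A reader might also take the Background, which says "SARS-CoV-2 can cause an explosive attack against the respiratory system, which is similar to major trauma", to mean that an injured patient would show the severe COVID-19 immune picture. That sentence compares the attack on the respiratory system with trauma when explaining ARDS. It says nothing about shared immune profiles.

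Three further objections have weight:

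- The primary hypothesis concerns severe infection, and no section names AS19 as the reference group. This limits the reach of the problem to comparisons that involve AS19.
- The same eligibility criteria apply to all four infected groups, so concurrent conditions may be present in each. This is why the direction of bias against ARD19 is uncertain.
- An article condenses a fuller protocol, and it does plan to collect comorbidities and clinical data. However, the source, the criteria, the sampling day and the type of comparison are stated here, and together they leave the gap.

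**Conclusion.** The point holds in a limited form. As written, the plan allows AS19 patients with another acute condition, samples them on the day of enrollment, and compares them without adjustment with controls who must be healthy and with the other severity groups. These comparisons are open to confounding by the reason for attendance.

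The size is unknown. The range of 0.05 to 0.7 SD rests wholly on the assumed fraction and shift, and its lower end would not matter. It should not be quoted as an estimate of bias in this study. The stricter criteria for controls are not an error in themselves, since they define a healthy control; what matters is the contrast with an unrestricted AS19 group. This is a cheap improvement to the analysis and does not invalidate the study.

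**What to change.** 1. From the existing hospital record, code the presenting diagnosis for every AS19 patient. Do the same for the mildly symptomatic group (PAU19), and ideally for all four groups so that concurrent conditions can be compared between them.
2. Report the AS19 comparisons with controls and with the other severity groups twice: for all AS19 patients, and for those without acute trauma, surgery, other infection or another acute inflammatory condition. Fix this coding before the immunological results are examined by group.
3. State how AS19 patients were identified.
4. If few patients remain after restriction, or if the two sets of results differ, describe the group as SARS-CoV-2-positive emergency attendees without COVID-19 symptoms and limit the conclusions accordingly.

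The cost is a review of about 30 records for AS19, or about 60 with PAU19, and up to 120 if all four groups are coded. The restricted AS19 analysis may have fewer than 30 patients and so wider intervals. According to Results, the clinical data set is complete and the immunological analysis is still under way, so there is time to do this. Recruiting asymptomatic patients from another source is no longer an option, because enrollment has closed.
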